# Minimisation of dialysis risk in hospital patients with chronic kidney disease (MinDial): study protocol for a multicentre, stepped-wedge, cluster-randomised controlled trial

**DOI:** 10.1186/s13063-024-08182-x

**Published:** 2024-06-07

**Keywords:** Chronic kidney disease (CKD), Kidney failure risk equation (KFRE), End-stage renal disease (ESRD), Estimated glomerular filtration rate (eGFR), Stepped-wedge design, Cluster-randomised trial (CRT)

## Abstract

**Background:**

Early identification of patients with chronic kidney disease (CKD) and advancing kidney insufficiency, followed by specialist care, can decelerate the progression of the disease. However, awareness of the importance and possible consequences of kidney insufficiency is low among doctors and patients. Since kidney insufficiency can be asymptomatic even in higher stages, it is often not even known to those belonging to risk groups. This study aims to clarify whether, for hospitalised patients with advanced chronic kidney disease, a risk-based appointment with a nephrology specialist reduces disease progression.

**Methods:**

The target population of the study is hospitalised CKD patients with an increased risk of end-stage renal disease (ESRD), more specifically with an ESRD risk of at least 9% in the next 5 years. This risk is estimated by the internationally validated Kidney Failure Risk Equation (KFRE). The intervention consists of a specific appointment with a nephrology specialist after the hospital stay, while control patients are discharged from the hospital as usual. Eight medical centres include participants according to a stepped-wedge design, with randomised sequential centre-wise crossover from recruiting patients into the control group to recruitment to the intervention. The estimated glomerular filtration rate (eGFR) is measured for each patient during the hospital stay and after 12 months within the regular care by the general practitioner. The difference in the change of the eGFR over this period is compared between the intervention and control groups and considered the primary endpoint.

**Discussion:**

This study is designed to evaluate the effect of risk-based appointments with nephrology specialists for hospitalised CKD patients with an increased risk of end-stage renal disease. If the intervention is proven to be beneficial, it may be implemented in routine care. Limitations will be examined and discussed. The evaluation will include further endpoints such as non-guideline-compliant medication, economic considerations and interviews with contributing physicians to assess the acceptance and feasibility of the intervention.

**Trial registration:**

German Clinical Trials Register DRKS00029691. Registered on 12 September 2022.

## Administrative information

Note: the numbers in curly brackets in this protocol refer to SPIRIT checklist item numbers. The order of the items has been modified to group similar items (see http://www.equator-network.org/reporting-guidelines/spirit-2013-statement-defining-standard-protocol-items-for-clinical-trials/).

**Table Taba:** 

Title {1}	Minimisation of dialysis risk in hospital patients with chronic kidney disease (MinDial): study protocol for a multicentre, stepped-wedge, cluster-randomised controlled trial
Trial registration {2a and 2b}.	DRKS00029691 [German Clinical Trials Register; registered on 12 September 2022; https://drks.de/search/en/trial/DRKS00029691]
Protocol version {3}	Version 3, November 2023
Funding {4}	This research is funded by the Innovation Fund of the Federal Joint Committee (G-BA) which is a decision-making body of the joint self-administration of physicians, dentists, hospitals and health insurance funds in Germany, grant number 01NVF20028.

Role of sponsor {5c}	This is an investigator-initiated trial. The study leader designed the funding application. All German statutory health insurances contribute to the Innovation Funds and the health insurance Knappschaft-Bahn-See provides the hospital information system (HIS). The funder played no role in designing the study and will not be involved in the data collection, analysis, interpretation of data, writing the report, or the decision to submit for publication. The funder takes part in the administrative management of the study as a controlling authority and reviews the results of the study with the purpose of deciding (together with representatives of the health insurance companies) whether the new form of health care shall be prospectively included in the fee schedule for billable health care services in Germany.

## Introduction

### Background and rationale {6a}

The prevalence of impaired renal function in the general population aged 45 years and older is about 10%. It is significantly higher in persons with hypertension, people with diabetes and those older than 70 years [1]. Chronic kidney disease (CKD), subsequent cardiovascular events and renal replacement therapies place a disproportionate burden on the healthcare system [2]. Early identification of CKD patients with advanced or rapidly progressive renal insufficiency and consistent specialist care can slow disease progression [3–5]: Risk factors for the progression of CKD, such as hypertension, diabetes and inadequate medication, can be better controlled with early specialist care. The incidence of medical complications and the resulting need for frequent hospitalisations are significantly reduced. Currently, no systematic CKD management has been established in Germany. A treatment guideline on the care of non-dialysis-dependent CKD patients in general practice was published in 2019 [https://www.awmf.org/leitlinien/detail/ll/053-048.html], but awareness of the importance and potential consequences of chronic renal disease is low among physicians and patients [6]. Because renal insufficiency can be asymptomatic even at higher stages, it is often unknown even in those from high-risk groups [7, 8]. Even when renal insufficiency is known, risk factors such as hypertension and diabetes are not adequately controlled [9, 10].

Identifying patients in need of specialised CKD management is therefore relevant both from a patient perspective and for economic reasons. Because CKD is a common comorbidity in hospitalised patients, cross-sector collaboration is useful in this setting to provide needs-based care for CKD patients. Structured referrals of hospitalised patients to the outpatient sector have resulted in improvements in various endpoints (mortality, rehospitalisation) for several conditions [11]. Increased attention to hospitalised patients with renal insufficiency and their referral to specialised care after discharge reduced mortality and the risk of end-stage renal disease (ESRD) in a Belgian study [12]. The German guideline for the care of non-dialysis CKD in general practice recommends referral of a CKD patient to a specialist when CKD is first diagnosed with an estimated glomerular filtration rate (eGFR) according to CKD epi of < 30 ml/min or with an eGFR of ≤ 60 ml/min with concomitant presence of albuminuria stage ≥ A2 (= albumin-creatinine ratio 30–300 mg/g), among others. The extent to which these recommendations are implemented for CKD patients in the context of primary care is not known. Studies on the referral practice of CKD patients have shown that, in addition to general practitioners’ lack of knowledge about CKD management and guidelines, the patient's attitude towards their disease can also lead to delayed referral to a specialist [13].

This study aims to clarify whether, for hospitalised patients with advanced chronic renal disease (specifically, with a Kidney Failure Risk Equation [KFRE] score of 9% to require dialysis within the next 5 years), a risk-based appointment with a nephrology specialist reduces disease progression. The KFRE score calculation was developed in independent Canadian patient cohorts in 2011 and validated internationally [14]. In studies of optimal care for CKD patients, the estimated 5-year ESRD risk has already been used for risk-based stratification of CKD patients for referral to a specialist in non-German populations [15, 16]. In its most commonly used form, it requires patient data on age, sex, eGFR and albumin/creatinine ratio (ACR). A formula without the use of ACR is also available and has been developed for validation for Dutch CKD patients [17].

The change in estimated glomerular filtration rate (eGFR) and control of risk factors such as hypertension and HbA1c in diabetic patients are used for assessment. Two groups of patients will be compared, one with the intervention of an appointment with a nephrologist, and one without this appointment in further routine care.

## Objectives {7}

The main objective of the study is to assess if risk-based discharge management related to the predicted 5-year risk of end-stage renal disease leads to needs-based specialist care for chronic renal disease and reduces further decline in renal function in terms of eGFR. Additional hypotheses are that the proportion of affected patients with uncontrolled hypertension—and/or uncontrolled HbA1c in diabetics—is reduced, and likewise, the medication that is not in line with guidelines or inadequate concerning renal function. Furthermore, the evaluation will include economic considerations and interviews with contributing physicians to assess the acceptance and feasibility of the intervention.

## Trial design {8}

The study is conducted in a stepped-wedge cluster-randomised design with 8 clusters, i.e. medical centres, after initially planning with 4 clusters (see Sample size section). All centres start with the recruitment of patients for the control group. After a time lag determined by randomisation in the stepped-wedge design, each cluster switches to the intervention phase. Ideally, equal numbers of patients should be recruited for control and intervention groups. The study aims to confirm the superiority of risk-based appointment management in CKD patients compared to the usual discharge management.

The stepped-wedge design and recruitment schedule are depicted in Fig. 1. Originally, nine recruitment phases of 50 days each were planned. In November 2022, the first recruitment phase (of control patients) was extended by 5 weeks to compensate for a slow start. Moreover, because of underrecruitment especially regarding the intervention group, it was decided in October 2023 to extend the recruitment by four additional phases.

**Fig. 1 Fig1:**
[figure not shown]
Modified stepped-wedge design of the MinDial study, depicting phases of recruiting into the control and intervention groups, respectively, and the follow-up schedule. In the stepped-wedge illustration, each row represents one of the eight medical centres (clusters). Four additional phases were incorporated later due to underrecruitment in the intervention group. The first follow-up applies only to patients in the intervention group

## Methods: participants, interventions and outcomes

### Study setting {9}

Patient recruitment takes place in North Rhine-Westphalia, Germany, in four hospitals of the miners’ health insurance company (’Knappschaft’) with a total of eight centres: Dortmund, Bottrop, Marl, Lünen, Kamen, Gelsenkirchen, Recklinghausen and Lütgendortmund. The hospitals are academic teaching hospitals of the University of Duisburg-Essen and the Ruhr University Bochum.

### Eligibility criteria {10}

#### Inclusion criteria

Age ≥ 18 yearsAdmitted to one of the participating hospitalsHealth insured with ‘Knappschaft-Bahn-See’Existing chronic renal disease (either already known and documented in the hospital information system as diagnoses ICD-10 N04.9, N17.99, N18.1–9, N19, R31, R80, or identified during hospitalisation (as distinct from acute renal failure))Risk of end-stage renal disease within 5 years according to KFRE score of at least 15% (date of laboratory determination before 20 June 2023) or at least 9% (since 20 June 2023), respectively; see the section ‘Participant timeline {13}’ for details on this change.Consent to contacting the general practitioner (GP) and specialists after dischargeGeneral state of health sufficient for study participation

#### Exclusion criteria

PregnancyPatients with ≥ 2 consultations with a nephrology specialist in the last 12 months before study inclusionInclusion in the MinDial study during a previous hospitalisation

### Who will take informed consent? {26a}

The study nurses inform eligible patients about the study and ask them if they consent to participate. If a patient has questions that cannot be answered by the study nurse, a study physician will be consulted before confirming the consent forms with the patient’s signature.

### Additional consent provisions for collection and use of participant data and biological specimens {26b}

In the informed consent form, participants may optionally consent to provide their health insurance data for further assessment following the study.

### Interventions

#### Explanation for the choice of comparators {6b}

The control group receives standard care, i.e. patients are discharged from the hospital as usual. This is the comparator of choice since the aim of the study is to assess if a risk-based appointment with a nephrology specialist reduces disease progression compared to current routine care.

#### Intervention description {11a}

The intervention consists of making an appointment with a nephrology specialist as part of hospital discharge management for patients in the intervention group. Control patients will not receive a study-related intervention. In detail, the intervention is organised as follows: A nephrology study nurse selects three nephrologists near the patient’s home. The patient selects a specialist from this list, with whom an appointment is then scheduled within the next three months after discharge. The study nurse at the respective site then passes the appointment on to the patient.

#### Criteria for discontinuing or modifying allocated interventions {11b}

If a study patient turns out to suffer from acute instead of chronic renal insufficiency, the intervention is cancelled for this patient. These patients are excluded from further follow-up.

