#### Strategies to improve adherence to interventions {11c}

One week after the agreed appointment, the study nurse calls the intervention patients to ask whether they have kept their appointment with the nephrologist and, if not, whether the nurse should arrange a new appointment.

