### Outcomes {12}

#### Primary endpoint

Difference in mean change in eGFR in ml/min/1.73 m^2^ (after chronic kidney disease epidemiology collaboration [CKD-EPI]) between the intervention and control group from baseline to 12 months after hospital discharge

The eGFR was chosen as the primary parameter because it is considered a good indicator for the assessment of kidney patients and has also been used in numerous nephrology studies over time [18].

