### Methods in analysis to handle protocol non-adherence and any statistical methods to handle missing data {20c}

Participants are analysed ‘as randomised’ (being cluster-randomised instead of randomised individually), independent of their medical treatment after hospital discharge. Participants without 12-month follow-up are reported in a CONSORT flowchart. Missing data of these participants are accounted for in the evaluation under the missing at random assumption.

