## Discussion

Since the start of participant recruitment, new insights were gained and several issues needed to be addressed. For instance, the composition of study participants differed noticeably from the intended target population, especially with regard to their age distribution. Hence, it was decided to decrease the cut-off value to identify patients with an increased risk of end-stage renal disease within 5 years from 15 to 9%. In general, recruitment is slower than expected. Beyond the adjusted cut-off value, counter-measures include extending the recruitment period by half a year, refreshing the training for the study nurses and improving the enrolment process. Since the recruitment target still had to be corrected downwards, two-sided testing was replaced by one-sided testing in the statistical analysis plan to increase power. It was also found that ruling out acute kidney failure is more time-consuming than anticipated. Potential study participants are sometimes not in the hospital long enough to be approached and enrolled after acute kidney failure has been ruled out. However, while this makes recruitment more challenging, it would not be a problem in routine care.

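### Ending follow-up of enrolled patients later judged to have acute kidney failure makes their 12-month eGFR missing for an outcome-related reason, with no stated rule to keep the two arms alike

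*Protocol article*

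**What the plan says.** The rule stands in the Protocol article, Criteria for discontinuing or modifying allocated interventions {11b}. It covers anyone already enrolled whose kidney failure proves not to be chronic. The appointment is called off, and for the later data the article states: "These patients are excluded from further follow-up". The section does not say who decides, on what data, up to what time, or what happens to a control patient, who has no intervention to cancel.

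The section on non-adherence and missing data {20c} sets an as-randomised analysis, whatever treatment follows once the patient has left hospital. Anyone lacking the one-year value is counted in the flowchart, and the handling is fixed in one sentence: "Missing data of these participants are accounted for in the evaluation under the missing at random assumption". It makes no exception for patients removed under {11b}.

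The primary endpoint compares the change in eGFR "between the intervention and control group from baseline to 12 months after hospital discharge". Table 1 shows eGFR at baseline and at the 12-month physician follow-up only. The primary model in {20a} contains intervention, period, baseline eGFR, age, gender and a random intercept for cluster.

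**The concern.** The rule acts after enrolment, in an unblinded trial, on a diagnosis closely tied to the outcome. A patient whose low hospital eGFR was acute can be expected to recover, so the change to 12 months would be a rise rather than a decline. Without the 12-month value, the patient either drops out of a model for change or is imputed from retained patients with similar baseline eGFR, age and gender. Most of those have chronic disease. Either way the recovery is not represented.

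If this happened equally in both arms, the contrast would not be biased. Equality is not secured, however. Between discharge and about month 11, planned study contact exists only in the intervention arm. Those patients have the nephrology appointment {11a}. One week after it, "the study nurse calls the intervention patients to ask whether they have kept their appointment with the nephrologist". They also receive the 3-month questionnaire; the caption of Fig. 1 says "The first follow-up applies only to patients in the intervention group". The first planned contact with control patients after discharge is the letter at about 11 months {18b}. An acute episode in a control patient thus has fewer occasions to come to the study's notice.

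Removing recovering patients mainly from the intervention arm would make the intervention look worse. At stake is a missed benefit in a trial whose planned power is already only 72.1%.

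**Working it through.** **The plan's own figures.** The second power update gives 72.1% one-sided power at 5% for a difference of 2.0 ml/min/1.73 m². The implied standard error is 2.0 / (z(0.721) + z(0.95)) = 2.0 / (0.586 + 1.645) = 0.897. At a difference of 2.23 this gives power Φ(2.23/0.897 − 1.645) = 80.0%, as the article states. The power figures are consistent; the concern is about bias.

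**Inputs that are assumed.** The article gives none of these:
- f, the share of enrolled patients who in truth have acute disease: 5% or 10%.
- R, their excess change in eGFR over chronic patients: 10 to 14, for example a gain of 8 to 12 against a loss of 2.
- c, the share of such patients detected and removed, which may differ by arm.

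**Formula.** The acute share retained in an arm is f(1 − c)/(1 − f·c). Bias (intervention minus control) = R × (retained share in intervention − retained share in control). With removal in the intervention arm only, this reduces to −f × R. Power under bias b is Φ((2.0 + b)/0.897 − 1.645), taking the true difference as 2.0.

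| Detection, intervention / control | f | R | Bias | Power |
|---|---|---|---|---|
| equal | any | any | 0 | 72.1% |
| 80% / 20% | 5% | 10 | −0.30 | 60% |
| 80% / 20% | 10% | 10 | −0.60 | 47% |
| 100% / 0% | 5% | 10 | −0.50 | 51% |
| 100% / 0% | 5% | 14 | −0.70 | 42% |
| 100% / 0% | 10% | 10 | −1.00 | 30% |
| 100% / 0% | 10% | 14 | −1.40 | 16% |

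One line in full, for f = 10%, R = 10 and detection 80% / 20%: 0.02/0.92 − 0.08/0.98 = 0.0217 − 0.0816 = −0.0599; times 10 gives −0.60. The power column holds the SE at 0.897 and so isolates the bias.

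**Cost of keeping these patients, on the same inputs.** If both groups have SD 4, the mixture has SD = √(16 + f(1 − f)R²):
- f = 5%, R = 10: √20.75 = 4.6
- f = 5%, R = 14: √25.31 = 5.0
- f = 10%, R = 10: √25 = 5.0
- f = 10%, R = 14: √33.64 = 5.8

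If the SE scales with the SD, it becomes 0.897 × 4.56/4 = 1.02 at the low end and 0.897 × 5.80/4 = 1.30 at the high end. Power at 2.0 is then about 62% and 46%. If the intervention did nothing for acute cases, the mean difference would also shrink to 2.0 × (1 − f), that is 1.9 or 1.8.

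**The case against.** Four objections carry weight.

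First, a reader might infer that {11b} and {20c} flatly contradict each other. They do not. {11b} ends follow-up and does not mention analysis, and {20c} provides for patients without follow-up. The phrase about later treatment does not cover a change of diagnosis. What stands is that the protocol itself creates missingness that its missing-at-random assumption is unlikely to cover.

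Second, a reader might infer that removals fall mainly on the intervention arm. The rule names no arm. Cancelling an appointment makes sense only before it takes place, which fits discovery in hospital, where both arms pass the same checks. Nor does the article describe a route by which a nephrologist's diagnosis reaches the study before month 12: the nurse's call asks about attendance, and the 3-month form is a patient questionnaire. Unequal removal is therefore plausible but not documented.

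Third, the Discussion's remark that "ruling out acute kidney failure is more time-consuming than anticipated" might be read as showing that acute cases are enrolled. In context it describes delay before enrolment and patients lost to recruitment. Chronic disease must also appear certain before consent, and doubtful cases go to a study physician (Participant timeline {13}). The number of later reclassifications may be small. Still, the existence of the rule shows that some are expected.

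Fourth, keeping acute cases costs precision. This stands in full, as the SD figures show. If removal were complete and equal in both arms, it would be unbiased and more efficient. The article offers nothing that secures either condition.

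**Conclusion.** The point holds as a defect in how the rule is fixed. Follow-up ends after enrolment, with allocation known, on a diagnosis that predicts the outcome and is absent from the model, without timing, decision-maker or a rule for control patients. This conclusion needs no assumed figure.

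The size of any bias is unknown. On the assumed inputs it lies between 0 with equal detection and 0.5-1.4 ml/min/1.73 m² with removal in one arm only. That upper range is 25-70% of the 2.0 target (0.5/2.0 to 1.4/2.0), but it is the extreme case and should not be read as an expected value. If detection is higher in the intervention arm, the bias runs against the intervention: the risk is a missed benefit, not a false claim of one.

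**What to change.** Reconcile {11b} with {20c}, in these steps:

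1. Delete the exclusion from follow-up. Collect 12-month eGFR and vital status for every consented patient through the existing request to GPs and nephrologists.
2. Keep all of them in the primary as-randomised analysis.
3. Allow exclusion for acute disease only on information available before discharge, by the same written rule in both arms, and name who applies it.
4. Record later reclassifications with date and source, report the counts by arm, and leave these patients out only in a sensitivity analysis.

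Whether the appointment itself should be cancelled is a clinical matter on which no view is taken.

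The cost is a short amendment and a few extra follow-up forms of a kind already routine for everyone else. There is also a statistical price: some dilution of the effect and, on the assumed inputs, an outcome SD of about 4.6-5.8 instead of 4. A consistent pre-discharge exclusion limits that price, because it keeps recognisable acute cases out of both arms alike. For patients already dropped, the 12-month values should be requested while they can still be obtained; no analysis can reliably replace them.
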